
### Inclusion criteria

Adult patients with a new diagnosis of IPF based on ATS/ERS criteria, confirmed by local MDD. A panel of 3 chest radiologists with ILD expertise will review each HRCT and patients will be included, if at least 2 out of 3 agree on a pattern of probable/definite UIP. A panel of 3 lung pathologists with ILD expertise will review each SLB and patients will be included, if at least 2 out of 3 agree on a pattern of probable/definite UIP.

### Exclusion criteria

ILD other than IPF.

Previous (rather than new) diagnosis of IPF.

Exclusion determined by the chest radiologists’ or lung pathologists’ panel.

Age < 18 years.

Patient not able to provide informed consent.

### MRC dyspnea score, pulmonary function tests and 6-min walk test

Dyspnea will be rated by using the MRCDS, which is a score designed to measure perceived respiratory disability, grading the effect of breathlessness on daily activities [24]. PFTs and 6-min walk test (6MWT) will be performed according to ERS/ATS guidelines [25–27] and the ATS guidelines [28], respectively. A standard reference equation will be used to calculate 6MWD percent predicted [19].

### High resolution chest CT scans

A quantitative fibrosis score on HRCT will be obtained at the time of diagnosis and on the repeat HRCT(s). The score will be calculated as previously described [12] by each of the chest radiologists, and the average of the scores will then be calculated for each scan. Interobserver variability will be evaluated. The presence and severity of coronary calcifications will be evaluated semi-quantitively as absent, mild, moderate or severe.

### Longitudinal follow-up

After diagnosis, patients are seen at 4-month intervals, for a period of 3 years in both the development and validation cohort. At each visit, MRCDS, PFTs and 6MWT will be obtained. Patients may be seen at closer intervals between visits, at the clinician’s discretion. After completion of the 3 years follow-up period, patients who are still alive without a LTx will continue to be followed regularly until required recruitment is completed, as long-term follow-up is part of secondary endpoints.

### Statistical analysis and sample size calculation

The distribution of variables considered will be analysed with Kolmogorov–Smirnov test. Interobserver variability among chest radiologists and lung pathologists will be assessed with Weighted kappa coefficients [29]. Survivors and non-survivors will be compared by using the unpaired t-test, or, for not normally distribute variables, with the Mann–Whitney U-test. To rule out multicollinearity and demonstrate that included variables are truly independent, variance inflation factors of the RISE components will be calculated [30]. Receiver operating characteristics analysis will be used to identify the most accurate cut-off values for each variable to predict endpoints. Multivariate analysis of significant predictors of endpoints will be conducted with the Cox proportional hazard model. Results will be summarized as hazard ratios. Once patients are listed for LTx, death and LTx become competing events. To account for the competing risks of LTx and death in the population of patients undergoing LTx assessment, the Fine-Gray competing risk regression model [31] will be used. This will identify variables significantly predicting independent survival status and results will be summarized as subdistribution hazard ratios. These represent the relative risk of dying prior to LTx. Survival will be further evaluated using Kaplan–Meier curves and the log-rank test. Sample size calculation for an observational, cohort study was conducted using the methodology described by Wang and Ji [32], with the assistance of a statistician. Using available, preliminary data on 109 patients, dropout rate, ratio of low RISE to high RISE, and mortality rates in low RISE and high RISE subgroups were determined. With a power (probability of detecting a real effect) of 90%, and with a conservative approach, a sample size of 125 patients for each cohort was determined to be required.

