We previously demonstrated that exertional dyspnea measured with the Medical Research Council dyspnea score (MRCDS), lung function and 6-min walk distance (6MWD) are significant and independent predictors of survival in IPF, with no observed collinearity among them [8]. The independence of the 3 domains (dyspnea, lung function, exercise capacity) was demonstrated in a prospective study [3] and in a multi-centre study as well [9].

The Risk Stratification Score (RISE) was first developed in a cohort of patients with IPF who were prospectively followed, and tested in another, retrospectively enrolled cohort. The acronym was later changed from ROSE to avoid confusion with “rapid onsite evaluation”. Capturing each of the 3 aforementioned domains, RISE is based on MRCDS, Composite Physiologic Index (CPI) and 6MWD. RISE was demonstrated to be superior to individual variables in predicting LTx-free survival [3]. We subsequently demonstrated that RISE was a reliable predictor of mortality in patients assessed for LTx [9], and also able to capture patient response to anti-fibrotic therapy better than the commonly used variables [11]. However, the main limitations of the 2012 study were the size of the prospective cohort, and the lack of prospective validation.

The current approach to the detection of progression of disease in IPF is largely based on forced vital capacity (FVC) changes and high-resolution chest CT scan (HRCT). We recently demonstrated that the prognostic accuracy of a decline of FVC combined with an increase of the extent fibrosis on HRCT (visual score) is far from being optimal, although the 2 variables are independent from each other [12]. This finding further strengthens the rationale for pursuing the development and validation of an integrated, multi-dimensional prognostic tool for IPF. As a more recent development, we tested a modified version of CPI against the original one, and found the new CALIPER-based CPI to be a stronger predictor of survival in IPF [13], making it a candidate component of the RISE.

The main objective of the study is to test and validate a modified version of the RISE in 2 separate cohorts of patients with IPF, prospectively followed from the time of diagnosis. To our knowledge, no previous, large scale, prospective, 3-year observational study has been conducted to validate a multi-dimensional staging system for IPF.

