1	I get short of breath when hurrying on level ground or walking up a slight hill
2	On level ground, I walk slower than people of the same age because of breathlessness
3	On level ground, I have to stop for breath when walking at my own pace
4	I stop for breath after walking about 100 m or after 5 min on level ground
5	I am too breathless to leave the house or I am breathless when dressing

The RISE (Table 2) will be first calculated, as previously described, on a scale from 1 to 3 [3]. However, a modified and improved version of the RISE will also be considered, using the CALIPER-revised CPI instead of the original version of CPI [13], and with a new 1 to 4 scale, which may allow for better stratification for mortality risk (Table 2). If superior to the previous version of RISE, the modified version will be tested for validation.

**Table 2 Tab2:** Risk Stratification Score (RISE) (revised)

RISE components: 1. MRCDS ≥ selected cutoff* 2. 6MWD % pred ≤ selected cutoff* 3. CPI ≥ selected cutoff*	RISE
No parameter met	0
One parameter met	1
Two parameters met	2
Three parameters met	3

MRCDS: MRC dyspnea score; 6MWD: 6-min walk distance; CPI: Composite Physiologic Index (CALIPER-revised version)

^*^selected cut-offs for each variable will be determined by receiver operating characteristics analysis (c-statistics)

Patients will be prospectively followed for a period of 3 years from the time of diagnosis and enrolment. All multi-dimensional scores will be calculated at 4-months intervals corresponding to each visit. A 2nd HRCT will be obtained at the 2-year visit, or sooner if clinically indicated, and as per clinicians’ discretion. The HRCT fibrosis score [12] will be then recalculated on the 2nd scan. Deaths, LTx, AEs and hospitalizations due to respiratory causes will be recorded. All protocol violations (missed visits, delayed visits, data not obtained at individual visits) will be systematically recorded. Every interruption or change in course of therapy will be recorded. When available, hemodynamic data from RHCs will be considered. Since 2D echocardiograms alone are unreliable in predicting the presence of APH in IPF [21], they will not be considered.

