The 6-min walk test is a well-established tool in the evaluation of chronic lung diseases, since it was demonstrated to correlate well with both quality of life [39] and post-therapeutic improvement [40], and to provide useful data for the prescription of ambulatory oxygen in ILDs [41]. Importantly, 6MWD was shown to also predict mortality in IPF: a 24-week decline of greater than 50 m [42] and the presence of desaturation during the test in patients with UIP [43] are both associated with an increase in risk of death at 1 year.

FVC decline significantly correlates with mortality in patients affected by IPF, even with a marginal decline of more than 5% at a 6-month interval [44]. Indeed, pirfenidone and nintedanib were approved for clinical use based on the data on FVC decline. FVC alone, however, has significant limitations in detecting progression of disease, as pointed out by several studies [6, 45]. The advantage of using the CPI is the combination of FVC with DLCO and FEV_1_. This index was developed against the morphologic extent of fibrosis on HRCT and considers the presence of coexisting pulmonary emphysema, which may be a confounding element in the interpretation of pulmonary function tests [15]. An improved version of the CPI was developed against the CALIPER-measured extent of fibrosis [13].

To predict the prognosis of such a complex condition as IPF, a multidimensional approach encompassing different domains is likely to better account for the severity of the disease, compared to a single variable approach [9]. A first step to identify the variables to associate in a multi-dimensional scoring system is to prove that each parameter is an independent predictor of the endpoint, and that there is no strong correlation or collinearity [30] among them. This has been proven in several studies for MRCDS, 6MWD and lung function measures [3, 8, 10], making them suitable candidates to be included in a prognostic score for IPF.

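### Variance inflation factors can check the RISE components for collinearity, but they cannot demonstrate that the components are independent, statistically or as predictors of survival.

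*Protocol article*

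**What the plan says.** The section on statistical analysis and sample size gives one calculation two purposes: "To rule out multicollinearity and demonstrate that included variables are truly independent, variance inflation factors of the RISE components will be calculated". It states no VIF limit.

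The components are named in the Background ("RISE is based on MRCDS, Composite Physiologic Index (CPI) and 6MWD"). Table 2 defines them as thresholded items, each worth one point: "RISE components: 1. MRCDS ≥ selected cutoff* 2. 6MWD % pred ≤ selected cutoff* 3. CPI ≥ selected cutoff". The table footnote says the cut-offs will come from receiver operating characteristic (ROC) analysis, and the CPI there is the CALIPER-revised version.

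Elsewhere the article treats independent prediction and absence of collinearity as two properties. The Background says that dyspnea score, lung function and walk distance "are significant and independent predictors of survival in IPF, with no observed collinearity among them". The Discussion says that a first step in choosing variables for a score is to "prove that each parameter is an independent predictor of the endpoint, and that there is no strong correlation or collinearity", and adds that earlier studies have established this for these measures.

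The statistics section also plans an analysis that uses the outcome: "Multivariate analysis of significant predictors of endpoints will be conducted with the Cox proportional hazard model". It does not say that the three RISE items enter that model together, and it does not connect the model to the independence statement.

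**The concern.** The second purpose asks the VIF for a conclusion it cannot give. A VIF is computed from the covariates alone. It describes how far the variance of a regression coefficient is inflated because one covariate can be predicted linearly from the others. A low value is compatible with clearly correlated components, and it says nothing about whether any of them is related to survival.

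What is at stake is a statement about the foundation of the score. RISE counts each met item equally, and the article presents independence of the three domains as the reason for combining them. Followed literally, the plan would let the study report its components as independent when two overlap substantially, or when one adds no prognostic information beyond the other two.

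**Working it through.** **Inputs from the protocol.** Three components (Background; Table 2) and 125 patients per cohort ("a sample size of 125 patients for each cohort was determined to be required"). The protocol gives no VIF, VIF limit or correlation, so there is no stated figure to reproduce.

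**Assumptions made here.** Limits of 2.5, 5 and 10; a common pairwise correlation r; normally distributed components. The dyspnea score is in fact a six-level grade (Table 1), so the results illustrate the behaviour of the check and do not predict this study's data.

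**Step 1: the VIF at a given correlation.** VIF = 1/(1 − R²), where R² comes from regressing one component on the other two. With three equally correlated components, R² = 2r²/(1 + r), so VIF = (1 + r)/[(1 − r)(1 + 2r)].

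- r = 0.5: 1.5/(0.5 × 2.0) = 1.50
- r = 0.7: 1.7/(0.3 × 2.4) = 2.36
- r = 0.8: 1.8/(0.2 × 2.6) = 3.46
- r = 0.9: 1.9/(0.1 × 2.8) = 6.79

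**Step 2: what each limit tolerates.** A limit L allows R² up to 1 − 1/L.

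- L = 2.5: R² up to 0.60, a common r up to 0.72
- L = 5: R² up to 0.80, r up to 0.86
- L = 10: R² up to 0.90, r up to 0.93

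**Step 3: chance that all three VIFs pass at n = 125** (5,000 simulated samples per row). The last column is the share of the same samples in which Bartlett's sphericity test, a direct test of zero correlation, rejects at 5%.

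| r | limit 2.5 | limit 5 | limit 10 | Bartlett rejects |
|---|---|---|---|---|
| 0.3 | 100% | 100% | 100% | 99.7% |
| 0.5 | 100% | 100% | 100% | 100% |
| 0.6 | 97% | 100% | 100% | 100% |
| 0.7 | 40% | 100% | 100% | 100% |
| 0.8 | 0.2% | 97% | 100% | 100% |
| 0.85 | 0% | 46% | 100% | 100% |
| 0.9 | 0% | 0.3% | 97% | 100% |

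At r = 0.3 and r = 0.5 the VIFs pass under every limit, in data where independence is rejected almost always.

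**Step 4: the items as scored.** If the VIF were computed on dichotomised items, it would be lower still. For median splits (an assumption), the correlation between items is (2/π) × arcsin(r). At r = 0.8 this is 0.59, giving VIF = 1.78. At r = 0.9 it is 0.71, giving VIF = 2.46, just under even the strictest limit considered.

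**Step 5: prognostic independence.** No limit helps here, because survival does not enter the calculation. As an illustration, 500 cohorts of 125 were simulated with r = 0.7 and only one of the three components prognostic (assumed log hazard ratio 0.7 per SD, baseline hazard 0.15 per year, 3 years of follow-up). The largest VIF was below 5 in 100% of runs. All three components were significant in a joint Cox model in 0.4%. The VIF did not reveal that two components added nothing; the outcome model rarely supported all three.

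**The case against.** The strongest defence is that the sentence starts with multicollinearity, so independence may simply mean that the components are not collinear, for which a VIF is a standard check. The article separates this from independent prediction and regards the latter as already shown. No component is added or dropped on the VIF result. A Cox model is planned, and which covariates it holds together is a detail a journal article may leave to the analysis plan. Nothing in the document suggests correlations of 0.7 to 0.8; the Background reports that no collinearity was observed.

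Much of this stands. The VIF is the right tool for the first purpose, outcome-based analysis is not absent, and large correlations are hypothetical. A reader might infer that the check would succeed almost whatever the data show. The documents do not support that: they state no limit, and with a limit of 2.5 the check would fail in most cohorts at r = 0.7, while even a limit of 5 would fail about half at r = 0.85. A reader might also infer that redundant items would go undetected. That is not established either, since the planned Cox model could reveal it if all three items were entered together.

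Two parts do not stand. The wording asks for more than absence of collinearity, and no unseen analysis plan can make a VIF demonstrate independence. Nor does the earlier evidence automatically carry over: the modified score uses the CALIPER-revised CPI and newly selected cut-offs, and it is the version put forward for validation if it proves superior.

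**Conclusion.** The point holds as a misassigned inference. Using VIFs to rule out multicollinearity is appropriate; using them to demonstrate independence is invalid under either meaning of the word. Low VIFs coexist with clear correlation (1.5 to 3.5 for r from 0.5 to 0.8), and they contain no information on survival.

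How often correlated components would pass depends on a limit the protocol does not state, so no single false-pass rate can be attached to the plan. The pass rates also rest on equal correlations and normal data. The conclusion that a VIF cannot show independent prediction rests on none of these assumptions.

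The consequence is limited to what the study may claim about its components. The primary endpoint, the sample size and the assessment of RISE as a whole score do not depend on the VIF. The change is worth making because the claim concerns the stated rationale of the score and correcting it costs little.

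**What to change.** Keep the VIF as a collinearity check only, and delete the second purpose from the sentence. Rest any claim of independent contribution on the Cox model already planned, for LTx-free survival, with all three RISE items entered together as dichotomised in Table 2. Report the adjusted hazard ratio and confidence interval for each item in the development cohort and, with the same cut-offs, in the validation cohort. Claim independent contribution only for items whose adjusted association supports it. Pairwise correlations of the components may be added as description.

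The cost is one reworded sentence and one small model per cohort, with no additional patients, visits or measurements. The downside is that an item may not show an independent contribution, in which case the study's claim would be less favourable.

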We hypothesize that both RISE at baseline and its longitudinal changes are the best predictors of survival in patients newly diagnosed with IPF followed for a period of 3 years, both in terms of sensitivity and specificity. The prognostic power of RISE will be compared to the current standard of care (individual pulmonary function tests, 6MWD, HRCT chest scan fibrosis score) and with other multi-dimensional scores as well, namely Gender-Age-Physiology (GAP) Index [14], CPI (both original and CALIPER-revised versions) [15, 16] and Mortality Risk Scoring System (MRSS) [17].

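### Judging RISE against its comparators on sensitivity and specificity at data-derived cut-offs discards information from the continuous comparators and can favour RISE

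*Protocol article*

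**What the plan says.** The last paragraph of the Background in the protocol article states the claim to be tested: "We hypothesize that both RISE at baseline and its longitudinal changes are the best predictors of survival", and gives the yardstick, "both in terms of sensitivity and specificity". It then names the competitors. "The prognostic power of RISE will be compared to the current standard of care", meaning individual pulmonary function tests, 6MWD and the HRCT fibrosis score, and "with other multi-dimensional scores as well, namely Gender-Age-Physiology (GAP) Index", followed by CPI in two versions and MRSS.

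The section on statistical analysis and sample size supplies the cut-offs: "Receiver operating characteristics analysis will be used to identify the most accurate cut-off values for each variable to predict endpoints". That sentence is not limited to the three RISE items. Their cut-offs are already covered by the footnote to Table 2, which is also the only place where c-statistics are mentioned.

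Table 2 builds revised RISE as a count of how many of three cut variables are met, giving four ordered levels, 0 to 3. The analysis methods named are Cox and Fine-Gray regression, Kaplan–Meier curves and the log-rank test. The form in which comparators enter the regression models is not given.

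**The concern.** Sensitivity and specificity exist only once a predictor has been split in two. FVC, DLCO, 6MWD, CPI and the fibrosis score are continuous or nearly so, and a single split throws away the ordering of patients on either side of it. RISE pools three splits and has four levels. If the comparators are judged at one cut and RISE is not, or if the cut costs RISE less, a comparator that predicts as well as RISE can look worse.

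The superiority claim is the core of the study. The article wants RISE used for clinical decisions and possibly as a trial endpoint, so an advantage that partly reflects the yardstick would mislead. Hazard ratios and survival curves do not correct this, because they are not a head-to-head comparison of discrimination.

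**Working it through.** **The plan's own figure.** The only relevant number printed is 125 patients per cohort at 90% power. It cannot be reproduced, because the mortality rates, the low-to-high RISE ratio, the dropout rate and alpha are not printed. With assumed 3-year mortality of 10–30% (low) and 40–60% (high), a high-RISE share of 30–50%, dropout of 0–20% and two-sided alpha of 0.05, the total runs from 34 to 1410. One combination that gives 125 is 30% versus 60%, 1:1, with 10% dropout. The present point does not depend on this figure; 125 is used below only as the cohort size.

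**Step 1: what one cut costs a continuous comparator.** Assumption: the marker is normal with equal variance in patients with and without the event, with means d standard deviations apart. Then:

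- full-scale AUC = Φ(d/√2), so d = √2 · z(AUC);
- the best single cut lies midway, where sensitivity = specificity = Φ(d/2);
- the AUC of a yes/no marker is (sensitivity + specificity)/2, here Φ(d/2).

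For AUC 0.70: z = 0.524, d = 0.742, Φ(0.371) = 0.645.

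| Full-scale AUC | After best single cut | Loss |
|---|---|---|
| 0.65 | 0.607 | 0.043 |
| 0.70 | 0.645 | 0.055 |
| 0.75 | 0.683 | 0.067 |
| 0.80 | 0.724 | 0.076 |

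**Step 2: does this change the ranking against RISE?** A simulation with 1,000 runs per setting; every input except the cohort size is an assumption. Each run has a development and a validation cohort of 125. Three standard-normal components have a common correlation of 0.3 or 0.5. The outcome is binary and logistic, with intercept −0.2 and log-odds 0.5 per SD for each component. RISE is the count of components above their ROC cut (maximum sensitivity plus specificity) from the development cohort. The comparator is the true linear predictor plus normal noise; the noise SD sets its quality. All AUCs are from the validation cohort.

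| Correlation, noise SD | RISE 0–3 | RISE one cut | Comparator full | Comparator one cut |
|---|---|---|---|---|
| 0.3, 0.8 (about equal) | 0.710 | 0.661 | 0.705 | 0.638 |
| 0.3, 0.5 (comparator better) | 0.710 | 0.661 | 0.731 | 0.659 |
| 0.5, 0.8 (about equal) | 0.737 | 0.683 | 0.728 | 0.657 |
| 0.5, 0.5 (comparator better) | 0.736 | 0.680 | 0.753 | 0.676 |

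Share of runs in which RISE has the higher AUC:

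| Correlation, noise SD | Both full scale | RISE 0–3 vs cut comparator | Both cut |
|---|---|---|---|
| 0.3, 0.8 | 56% | 95% | 68% |
| 0.3, 0.5 | 28% | 91% | 52% |
| 0.5, 0.8 | 59% | 97% | 72% |
| 0.5, 0.5 | 30% | 95% | 54% |

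In the first row, cutting costs RISE 0.710 − 0.661 = 0.049 and the comparator 0.705 − 0.638 = 0.067. Cutting both therefore still helps RISE, though far less than cutting only the comparator.

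**Step 3: does RISE have a real advantage as well?** With the comparator set to one RISE component on its full scale, RISE has the higher AUC in 73% of runs at correlation 0.3 (0.709 versus 0.683) and 69% at correlation 0.5 (0.740 versus 0.723).

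**The case against.** The strongest reply is that the article never says the comparators are compared only as yes/no variables. Identifying a cut-off is not the same as analysing by it. ROC analysis itself uses the full scale, the survivor versus non-survivor tests use uncut values, and the covariate form in the Cox and Fine-Gray models is open. In the Table 2 footnote similar wording refers only to the three RISE items. This stands: a reader might infer that every comparator is certain to be reduced to one cut, and the text does not support that. The reply does not remove the stated yardstick, which needs a cut, or the breadth of the ROC sentence, which covers prediction of endpoints in general.

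Second, sensitivity and specificity require a cut on RISE too, and its items are already cut. This also stands and shrinks the effect considerably, to the last column of the second simulation table. No section describes four-level RISE set against a cut comparator; that column is the worst case.

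Third, a reader might infer that RISE would look best only because its competitors lost their scale. That is not supported: RISE combines three domains, and Step 3 shows a real advantage over a single component under the assumed settings. Nor does the loss apply equally to every comparator. The Discussion describes GAP as three stages, so it is not a continuous test being split.

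Fourth, a reader might see a defect in sizing the study on low versus high RISE. It is a planning simplification and does not fix how RISE will be analysed.

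Finally, a condensed article may leave the choice of discrimination index to the full plan. Its absence alone would be no finding. The point rests on what the article does state.

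**Conclusion.** The point holds in a limited form. The article names sensitivity and specificity as the basis for calling RISE the best predictor, provides data-derived cut-offs for each variable, and states no comparison on the comparators' original scales. Such a yardstick discards information from continuous comparators, about 0.04 to 0.08 in AUC for full-scale AUCs of 0.65 to 0.80, and can favour RISE.

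How far it favours RISE depends on a choice the article leaves open. At correlation 0.3 and against a truly better comparator, RISE comes out ahead in 28% of runs on full scales, 52% with both cut, and 91% with only the comparator cut. These sizes rest on the binormal model and the simulation settings, not on data from the study. They show direction and plausible size, and do not predict the study's result.

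**What to change.** In the hypothesis paragraph of the Background and in the statistical section:

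- limit ROC-derived cut-offs to defining the three RISE items;
- keep each comparator on its original or published scale, and RISE as its ordered 0–3 score;
- make the main comparison the difference between RISE and each comparator in C-index or 3-year time-dependent AUC, with a bootstrap confidence interval, in the validation cohort;
- report sensitivity and specificity as descriptive only, at cut-offs fixed in the development cohort.

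This changes analysis wording only. It needs no extra patients, visits or measurements, since all the variables are already collected. The price is that the reported advantage of RISE may be smaller.

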### Primary endpoint

Three-year, LTx-free survival from the time of diagnosis, measured as the time between diagnosis and death from any cause, or LTx. Once they receive a LTx, patients will be censored. Since mortality and LTx are competing events, a Fine-Gray competing risk regression analysis will be used. Please refer to the statistics section for details.

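### The ROC analysis that sets the RISE cut-offs has no stated way to handle patients transplanted or lost before 3 years, which leaves the accuracy figures open to bias

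*Protocol article*

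**What the plan says.** All of this is in the protocol article.

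- **Endpoint (Primary endpoint).** "Three-year, LTx-free survival from the time of diagnosis, measured as the time between diagnosis and death from any cause, or LTx". The next sentence reads "Once they receive a LTx, patients will be censored", and the one after it "Since mortality and LTx are competing events, a Fine-Gray competing risk regression analysis will be used".
- **Cut-offs (Statistical analysis and sample size calculation).** "Receiver operating characteristics analysis will be used to identify the most accurate cut-off values for each variable to predict endpoints". The footnote to Table 2 in Methods and design ties this to the score: "selected cut-offs for each variable will be determined by receiver operating characteristics analysis (c-statistics". RISE is then the number of components past their cut-off.
- **Accuracy (Background, final paragraph).** RISE is hypothesised to be the best predictor in patients "followed for a period of 3 years, both in terms of sensitivity and specificity". Its prognostic power is to be compared with single measures and with GAP, CPI and MRSS.
- **Group comparison (Statistical analysis).** "Survivors and non-survivors will be compared by using the unpaired t-test", or by Mann-Whitney where the data are not normal.
- **Methods that do handle censoring (Statistical analysis).** "Multivariate analysis of significant predictors of endpoints will be conducted with the Cox proportional hazard model", together with Fine-Gray, Kaplan-Meier and log-rank.
- **Dropout (Statistical analysis).** A dropout rate from 109 preliminary patients fed the sample size. Its value is not given.

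**The concern.** An ordinary ROC curve sorts every patient into event or no event by the horizon. A patient transplanted at month 10 or lost at month 20 has no observed 36-month vital status, so someone must call that patient a survivor or leave the patient out. If transplant or loss is related to severity, either choice distorts sensitivity, specificity and the AUC, and a larger sample does not remove the distortion.

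The ROC step is not decorative here. It fixes the three cut-offs that make up the score, and sensitivity and specificity are the terms of the hypothesis. The article names censoring-aware methods for regression and survival curves but none for this step. The status of a transplanted patient cannot be read from the endpoint definition either, because that definition treats LTx in two ways.

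**Working it through.** **The plan's own figure.** The only computed figure is 125 patients per cohort at 90% power. The mortality rates, the ratio of low to high RISE, the dropout rate and alpha are not given, so it can be neither reproduced nor refuted. It is not in dispute here and is used only for sampling error.

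**Inputs.** The 3-year horizon, the endpoint and the 125 come from the article. It gives no death, LTx or dropout rates, so these are assumed:
- 3-year death 45%, with marker log hazard ratio 0.9 per SD
- LTx 10% or 20%, log hazard ratio 0.7 per SD unless stated
- dropout 0%, 10% or 20%, unrelated to the marker except in row c (log hazard ratio 0.5 per SD)

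These are rates before the processes compete. With 10% LTx and 10% dropout, 6.0% of patients are seen to be transplanted first and 7.0% lost first, so 13.0% lack a 3-year death status (about 16 of 125). With 20% and 20% it is 11.8% + 13.7% = 25.5% (about 32 of 125).

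**Method.** 500,000 patients per scenario, with exponential times to death (D), LTx (L) and dropout (C), each with rate λ·exp(βx).
- AUC = P(marker of a case > marker of a control).
- The cut-off maximises sensitivity + specificity − 1.
- True status for death is D ≤ 3 had neither LTx nor dropout intervened. For the composite it is min(D, L) ≤ 3.
- The weighted (IPCW) version gives each patient with known composite status the weight 1/G(min(T, 3)), where T = min(D, L) and G is the probability of not yet having dropped out. For 10% dropout the rate is −ln(0.90)/3 = 0.035 per year, so no weight exceeds 1/0.90 = 1.11.

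**AUC, with difference from the true value**

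| | Target | LTx / dropout | True | Called survivors | Dropped | IPCW |
|---|---|---|---|---|---|---|
| a | Death or LTx | 10% / 0% | 0.778 | 0.778 (0) | 0.778 (0) | 0.778 |
| b | Death or LTx | 10% / 10% | 0.778 | 0.771 (−0.007) | 0.779 (+0.001) | 0.778 |
| c | Death or LTx | 10% / 20%, marker-related | 0.778 | 0.743 (−0.035) | 0.787 (+0.009) | 0.784 |
| d | Death | 10% / 10% | 0.779 | 0.754 (−0.025) | 0.785 (+0.006) | not run |
| e | Death | 20% / 20% | 0.779 | 0.731 (−0.048) | 0.791 (+0.012) | not run |

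In rows a-c only dropouts need classifying, because LTx is an event. In rows d-e both LTx and dropout do.

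**Specificity at the chosen cut-off.** When LTx and dropout are called survivors it falls from 0.736 to 0.704 in row d (−0.032) and to 0.658 in row e (−0.078).

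**Sensitivity to the link between LTx and severity (death, LTx 20%, dropout 10%).** With log hazard ratio 0.9 the AUC is 0.726 when called survivors (−0.053) and 0.790 when dropped (+0.011). With no link it is 0.761 (−0.018) and 0.782 (+0.003).

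**Cut-offs.** In rows a-e the two ordinary-ROC rules move the cut-off by about 0.05 SD at most (row e: 0.131 to 0.083). A separate simulation with three correlated components gave up to about 0.15 SD.

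**Sampling error at 125 patients (500 repeats).** The SD is about 0.04 for the AUC and 0.27-0.31 marker SD for the cut-off. In row e the choice of rule alone moves the AUC by 0.791 − 0.731 = 0.060, more than its sampling SD.

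**The case against.** The strongest reply is that the article never says the ROC is a plain binary one, nor that transplanted or lost patients count as survivors. Time-dependent ROC fits the same words, and a condensed article may leave the variant to the full plan. This stands in part: ordinary ROC is an inference. It is still the natural reading, since the same section names a censoring-aware method for every other outcome analysis that needs one. The double treatment of LTx is in the text itself and is not an omission.

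The second reply is that a fixed 3-year horizon with LTx as an event and complete status gives no bias at all. Row a confirms this. But the article also expects dropout, censors LTx, and tests RISE as a predictor of mortality, so that favourable case cannot be taken as the plan.

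The third is that cut-off shifts are swamped by sampling error at 125 patients. That stands, and the point rests on the accuracy figures.

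A reader might infer four further things that the documents do not support:
- **That the t-tests distort the cut-offs or accuracy.** The article gives them no role in either.
- **That c-statistics are the stated measure for comparing scores.** The Table 2 footnote links them only to cut-offs.
- **That the two cohorts differ in access to LTx.** Two centres are named, but cohorts are not assigned to centres and no difference in access is described.
- **That transplanted patients are simply the sickest.** The Discussion stresses a window in which patients remain eligible, so the link with severity is an assumption, varied above.

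**Conclusion.** The concern holds in a limited form. The ROC step that builds RISE, and the 3-year sensitivity and specificity, have no stated censoring-aware form, while the endpoint has expected dropout and an unresolved role for LTx.

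Under the assumed rates, the AUC for death is understated by about 0.025-0.05 if transplanted and lost patients are called survivors, and overstated by about 0.006-0.012 if they are dropped. For death or LTx the range is from no bias to about −0.035. Every size depends on assumed death, LTx and dropout rates and on a classification rule that the article does not give. The figures for death also take as truth the deaths that would occur without LTx.

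A reader might go further and conclude that the cut-offs and accuracy figures will be biased. The documents do not support that: the sign and size turn on the unstated rule, and one admissible reading gives no bias. The Cox, Fine-Gray and Kaplan-Meier analyses are not affected by this point.

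**What to change.** 1. Reconcile the Primary endpoint section: state for each target whether LTx is an event or a competing event, and remove the conflict with censoring at LTx.
2. Name time-dependent (cumulative/dynamic) ROC at 36 months with inverse-probability-of-censoring weights. LTx is an event for LTx-free survival and a competing event for death before LTx. For the latter, say whether transplanted patients belong among the controls.
3. Let the weights depend on baseline severity. In row c, weights that ignored the marker left the AUC at 0.784 against a true 0.778.
4. Use these curves both to select the cut-offs and to compare RISE with the other scores.
5. Label the survivor/non-survivor tests as descriptive only, and say who is in each group.

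Cost: protocol wording, standard software and a little more analysis work, with no new data. Intervals become slightly wider through weighting.

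Suggested text: *Cut-offs and accuracy will be estimated by cumulative/dynamic time-dependent ROC at 36 months, weighted for the inverse probability of remaining uncensored given baseline severity. LTx is an event for LTx-free survival and a competing event for death before LTx.*
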